**Fig. 3 Fig3:**
[figure not shown]
Overview of the BRIDGE intervention including an inpatient preparatory phase, an outpatient main phase followed by a maintenance and follow-up phase. The intervention is prepared during the two inpatient sessions and participants are allocated to either the basic or intensive version based on the severity of depressive symptoms (MADRS score ≥ 20 for the intensive version). Both versions consist of blended care comprising home visits, video consultations and home-based guided PE videos and differ only in the number of consultations (basic = 8 x obligatory consultations: 2 x home visits and 6 x video consultations, 12 guided PE videos; intensive = 12 x obligatory consultations: 4 x home visits and 8 x video consultations, 12 guided PE videos). The intensive version includes three additional monthly check-up calls following the intervention

### Behavioral activation component of the BRIDGE intervention

The BRIDGE intervention incorporates a structured BA framework, specifically adapted to the psychosocial and functional needs of older, multimorbid individuals with depressive symptoms. The BA component emphasizes the systematic identification of and engagement in rewarding activities to counteract depressive symptomatology in line with the behavioral theory of depression [47] by use of specific Behavioral Change Techniques (BCT). BCT´s are following the BCT taxonomy v1 [48] comprising Goal setting (behavior) [1.1] (e.g., agree on engaging in three daily positive activities and reach agreement about the goal), and Action planning [1.4] (e.g., written scheduling of pleasant activities including physical exercise videos using the BRIDGE workbook). Self-monitoring of behavior [2.3] (e.g., by ticking off in the BRIDGE workbook if the planned activities have been performed), and Self-monitoring of outcome(s) of behavior [2.4] (e.g., daily rating of the current mood state on a 7-point visual analogue scale (VAS) using facial expressions ranging from “very unhappy" to "very happy” in the morning and evening automatically provided by the BRIDGE device; rating of mood changes due to a performed activity on a 7-point VAS using facial expressions ranging from “very unhappy" to "very happy” in the BRIDGE workbook), along Feedback on outcome(s) of behavior [2.7] and Social reward [10.4] (e.g., monitoring of pleasant activities including physical exercise videos, mood monitoring and discussion of changes with the BRIDGE team). Moreover, Social support practical [3.2] and emotional [3.3] (e.g., during home visits and video consultations), Information about emotional consequences [5.6] (e.g., effect of physical exercise on mood), Information about health consequences [5.1] (e.g., effect of physical exercise on physiological fitness) provided by the BRIDGE team. Additionally, Instruction on how to perform the behavior [4.1] (e.g., written and verbal instructions provided in the BRIDGE workbook and via the BRIDGE team), Prompts/cues [7.1], Habit formation [8.3], and Self-reward [10.9] in form of the Tiny Habits^®^ method [49]). The BCT´s are completed by Self-talk [15.4] (e.g., self-formulated positive sentences written into the BRIDGE workbook after completing an activity or coping with barriers) and Verbal persuasion about capability [15.1] by the BRIDGE team during home visits and video-consultations (e.g., telling the participants that they can successfully perform the desired behavior, arguing against self-doubts and emphasizing their abilities and progress) and overall Reduce negative emotions [11.2] (e.g., advising participants to use BA components and PE videos to enhance or stabilize their mood) 

**Fig. 4 Fig4:**
[figure not shown]
BRIDGE study flow chart

In addition to the use of BCTs, one prominent feature of BA in the BRIDGE intervention is its integration of the Tiny Habits^®^ method [49], which is based on evidence from the Positive Experience Program (PEP) for Depressed Older Adults [50]. While BA emphasizes the value of increasing engagement in everyday positive activities to lift mood, the Tiny Habits^®^ method is a straightforward, evidence-based framework for integrating new behaviors into existing routines. It employs a structured approach called Tiny Habits Recipes, which follow the format: “*After [Anchor Moment]*,* I will [Tiny Behavior].*” The Anchor Moment refers to an action that is already reliably part of one’s daily routine, serving as a cue for the new behavior. The Tiny Behavior is the desired action, scaled down to require minimal time and effort. For example, a recipe might be: “*After I brush my teeth in the morning*,* I will do five shoulder rolls to mobilize my shoulders*”. To reinforce the new behavior, a celebration is performed immediately afterward, such as thinking or saying out loud, “*It feels great to be mobilized!*” or patting oneself on the shoulder, to evoke positive emotions and a sense of success. This reinforcement strengthens the connection between the Anchor Moment and the Tiny Behavior, promoting automation of BA. The latter part reinforces the immediate awareness of the synergies between activity and mood. Additionally, the method involves a focus on behaviors that individuals genuinely want to adopt rather than those they feel they should or must do. Research supports the effectiveness of the Tiny Habits^®^ method (e.g [51]). It utilizes implementation intentions [52], which have been shown to enhance goal achievement by increasing the mental accessibility of cues (Anchor Moments) and solidifying the link between cues and planned actions (Positive Tiny Behaviors). Moreover, small, simple, and intrinsically enjoyable behaviors are expected to be more consistently performed and more easily formed into habits. The behavioral activation methods of the BRIDGE program are especially well-suited for multimorbid older adults experiencing subsyndromal or clinical depression, for whom low burden and positive reinforcement strategies are critical to maintaining engagement and promoting emotional well-being.

The inclusion of guided, video-based PE further strengthens the activation framework of the BRIDGE program and is supported by educational materials that promote safe and accessible home-based exercise. These strategies are intended to help participants to maintain behavioral and physical activation even when motivation or mood decline.

### Physical exercise component of the BRIDGE intervention

As a core pillar of the BRIDGE intervention, physical activity is promoted through the systematic implementation of daily video-guided exercise sessions. The exercise sessions will be performed independently by participants at home using the BRIDGE device (tablet device) to play the videos. The videos were developed specifically for the BRIDGE intervention based on the expertise of exercise scientists and psychologists, oriented towards established physical exercise programs for older adults such as the Otago Exercise Program [53, 54], VIVIFRAIL [55], PROMOTE [56, 57], and PROGRESS [58]. They are designed to support both physical and mental health and are tailored specifically for older, multimorbid adults experiencing depressive symptoms and are supplemented by mind-body exercises (e.g., yoga exercises, progressive muscle relaxation, and breathing meditation). Exercises are designed to be effective in reducing depressive symptoms [59] also in this population [17, 60–62]. Participants will receive a total of 12 guided PE videos, with one new video per intervention week. The PE videos are available in a standing and sitting variant, depending on individual physical abilities (e.g., balance, walking), as assessed using the SPPB [41] at T1 assessment. Participants with an SPPB score below the cut-off of 7 will be assigned to the sitting PE videos. Each exercise video lasts approximately 20 min and follows a standardized structure, consisting of a welcome and warm-up phase, a main training phase, and a cool-down phase with a relaxation focus. The PE in the videos are verbally instructed (BCT: Instruction on how to perform the behavior [4.1]) and visually demonstrated (BCT: Demonstration of the behavior [6.1]) by a middle-aged female instructor, serving both as a facilitator and a role model (BCT: Behavioral practice and rehearsal [8.1], e.g., prompt participants to include physical exercises in their daily life; [12.6] Body changes, e.g., prompt aerobic, strength, and coordination exercises, and relaxation training). In more detail, the exercise videos are grounded on a multicomponent training approach that integrates whole-body strength training, endurance exercises, flexibility, coordination activities, dual-task exercises (e.g., simultaneous motor-cognitive tasks), and elements of mind-body exercises. In the latter, a distinct emphasis is placed on the mind-body connection, which is operationalized through integrated elements of relaxation and mindfulness (e.g., breathing meditation, progressive muscle relaxation). Mind-body exercises typically include inward-focused attention on breathing and body awareness (proprioception), which may facilitate antidepressant effects [60]. Accumulating evidence suggests that mind-body exercise approaches exert the most robust antidepressant effects in older adults [16, 63]. The overall exercise content is intentionally progressive: Over the 12-week course of the intervention, each new video incrementally increases the physical and cognitive demands, either through the introduction of novel exercises or the modification and intensification of previous ones. This structured progression is aimed to reduce depressive symptoms and enhance physical fitness, which seems to be more effective with more intense exercise [16, 64], and to promote neuroplasticity through ongoing cognitive-motor stimulation [65]. To support motivation, adherence, and emotional engagement, all videos are narrated by the same female instructor, who delivers scripted personalized and encouraging messages, reinforcing participants’ self-efficacy and mindfulness and promoting a self-empowering narrative throughout the exercise videos. Taken together, the structure, content, and scripted instructions facilitate safe participation while providing a familiar and predictable format that supports adherence over time. Although participants engage with the exercise videos independently, their experience is closely monitored and reflected upon during home visits and video consultations, during which members of the BRIDGE team review adherence and feedback related to the video exercises (assessed via the enna.care app) and identify and tackle barriers to participation, for example by adjusting the physical activity component as needed based on individual abilities (e.g., an exercise part cannot be performed due to a physical impairment or pain), safety considerations, or changes in physical health.

This dual approach — self-guided yet therapeutically supported — encourages autonomy while maintaining clinical monitoring, thereby maximizing engagement and potential treatment effects.

### Intervention delivery: the BRIDGE team

An essential component of the BRIDGE intervention is the establishment of an interdisciplinary and multiprofessional BRIDGE team at each study center. The BRIDGE team consists of a nurse, a psychologist, and a exercise scientist. This interprofessional structure will be maintained throughout the intervention period to ensure the optimal and continued integration of nursing, psychological, and physical activity expertise in addressing the complex needs of older adults with depressive symptoms and multimorbidity.

Prior to implementation, all BRIDGE team members will complete a standardized, role-specific, and interprofessional training program, which includes pre-recorded instructional videos and interactive online sessions based on a structured intervention manual. The training will ensure consistent delivery of the intervention across study sites and professional roles.

The BRIDGE nurse will serve as the primary contact person for participants and as the main intervention provider. Responsibilities of this role include home visits, digital video consultations, facilitation of an activity schedule, encouragement of mood monitoring, implementation of clinical assessments (T1 – T5), and documentation of intervention components as well as clinical observations. The nurse will establish a relationship of trust and cooperation with participants, characterized by empathy and individually tailored support. This includes monitoring depressive symptoms, promoting BA, and facilitating access to further services (e.g., exercise groups, community centers). In acute situations (e.g., psychological crises or serious physical complaints), the nurse will coordinate with team members to initiate appropriate emergency procedures. The exercise scientist will support and supervise the nurse in the assessment of physical functioning (e.g. handgrip strength, SPPB), advise on individual tailoring of the exercise content across the intervention, and educate participants on the health benefits of PE. They may also offer direct patient consultation if needed (see Fig. 4) and contribute to decision-making during physical health emergencies in accordance with their professional scope. The psychologist will ensure both quality and fidelity of the BA. They will support the nurse in the assessment of psychological symptoms and cognitive and global functioning while also supervising the nurse in terms of adapting and individually tailoring the BA to fit specific patient needs. Additionally, the psychologist will provide psychoeducational information on depression and the principles of BA for the participants. The psychologist may also provide participants with direct consultations if needed (see Fig. 4). In the case of a mental health crisis, the psychologist will be responsible for an initial risk assessment and will work with the team and healthcare providers to coordinate an appropriate and timely response in accordance with German emergency medical regulations.

#### Interprofessional collaboration

Interprofessional collaboration within the BRIDGE team is an integral part of the BRIDGE intervention. All team members will complete joint training and engage in structured interprofessional meetings during the intervention period. These weekly meetings will enable shared decision-making, review of clinical findings, and discussion of implementation barriers (e.g., reduced motivation, comorbid physical conditions). Each team member will contribute equally to these discussions, fostering collaborative learning and integrated care delivery. Additionally, each BRIDGE team will participate in monthly online supervisions, provided in an individual setting (focusing on one BRIDGE team) and a group setting (including all BRIDGE teams across study centers), led by two BRIDGE project team members (an exercise scientist and a psychologist).

### Control group (CG)

Participants allocated to the CG will receive usual care consisting of health and care services routinely available to older adults in the German healthcare system. Following the final assessment (T5, nine months post-discharge), participants will be compensated with a €30 voucher redeemable for a large variety of goods online (wunschgutschein.de), whereas participants in the IG will not receive monetary compensation. 

### Outcome evaluation

Five assessment time points (T1 – T5) are planned to assess the short- and medium-term effects of the BRIDGE intervention. These time points are identical for the IG and the CG. Table 1 provides an overview of the outcome evaluation endpoints and their operationalization, including the corresponding data sources. For most endpoints, the post-discharge time point T2 (start of the intervention in the home) is used as the baseline, since the (partial) inpatient setting at T1 could bias the baseline assessment. The primary endpoint is defined as the maintenance or improvement of (partial) inpatient treatment outcomes regarding depressive symptoms from post-discharge (T2) to six months post-discharge T4 (at the end of the check-up calls in the intensive version). Depressive symptoms will be assessed at all time points (T1 through T5) via both self-report (e.g., HADS) and clinician rating (e.g., MADRS) to additionally evaluate the secondary endpoint of depressive symptom reduction over the full follow-up period. Physical functioning, physical activity, quality of life, perceived stress, and emotional well-being will also be assessed at all five time points (T1 to T5). To prevent training effects, cognitive functioning will be measured at T2 and T3 (end of the intervention in the home) only; no further assessments of cognitive functioning are planned. The number of days of (partial) inpatient days after the initial discharge will be documented by the BRIDGE team at T3, T4, and T5.

### Process evaluation

The process evaluation includes surveys and interviews with participants as well as an online survey and focus groups with the BRIDGE team members as intervention providers. Both primary data (from participants and BRIDGE teams) and secondary data (eCRF and usage of BRIDGE device) will be analyzed.

### Evaluation by participants

Acceptance and satisfaction with the BRIDGE intervention will be assessed at the end of the intervention through self-report questionnaires at T3 and T4. The fidelity of the BRIDGE intervention will be documented via the eCRF, supplemented by usage data recorded by the BRIDGE device (e.g., frequency and duration of physical exercise videos used). Custom-developed questionnaires, informed by established patient satisfaction instruments (e.g. [66, 67]), will be used to evaluate specific components of the intervention such as the blended care approach (mix of home visits and video consultations), physical exercise, workbook use, and the digital components.

Additionally, an in-depth process evaluation will be conducted, exploring the subjective change processes perceived by participants in their daily lives as a result of their participation. In the first step, a subset of participants from the intervention group will be invited to take part in structured interviews after completing the intervention (after T3) to explore their subjective experiences. To achieve theoretical saturation, approximately 20 participants are expected to be required. For pragmatic reasons (see below), recruitment will focus on those who complete the intervention the earliest, ensuring variation in gender, hospital site, intervention format (basic vs. intensive version), and degree of physical impairment. The interviews will be audio-recorded and fully transcribed. Using qualitative content analysis [68], categories will be developed inductively from the textual material. These categories will represent different types of subjective change processes (e.g., “rediscovering resources,” “defining life goals”). Based on the categories, an instrument will be developed to conduct a short, problem-centered interview, which will then be used with all IG participants who did not take part in the initial 20 interviews. This interview will be administered at the 3-month follow-up (T4; six months post-discharge and the end of the check-up calls in the intensive version).

### Evaluation by BRIDGE teams

An online survey of all BRIDGE team members will be conducted during the final quarter of their study involvement (or upon exit, but no earlier than six months after the project’s start). The survey will assess acceptance and perceived utility of the care model for routine practice. Additionally, two focus groups will be held to explore interdisciplinary and cross-sector collaboration as well as the potential to integrate the BRIDGE intervention into existing care structures in Germany. Each group will include BRIDGE team members of all sites (~ 21 participants in total), ensuring representation across regions (urban and rural). Topics will be derived from project experience and may include urban–rural disparities in care infrastructure, the impact of initial treatment setting (e.g., geriatrics vs. psychogeriatrics), and differences between partial and full inpatient groups.

### Health economic evaluation

The health economic evaluation aims to assess the cost-effectiveness of the BRIDGE intervention compared to usual care from a healthcare system perspective. A cost-effectiveness analysis (CEA) will be conducted using the incremental cost-effectiveness ratio (ICER), which relates the difference in total costs between the IG and the CG to the difference in observed benefits. Effectiveness will be derived from the primary outcome and selected secondary outcomes.$$\:ICER=\frac{IG\:costs-CG\:costs}{\mathrm{I}\mathrm{G}\:\mathrm{b}\mathrm{e}\mathrm{n}\mathrm{e}\mathrm{f}\mathrm{i}\mathrm{t}-\mathrm{C}\mathrm{G}\:\mathrm{b}\mathrm{e}\mathrm{n}\mathrm{e}\mathrm{f}\mathrm{i}\mathrm{t}}$$

## Operationalization of costs

Costs are primarily operationalized via healthcare and long-term care utilization. Primary data on healthcare and long-term care utilization will be collected through structured interviews conducted by the BRIDGE team six months post-discharge (T4). The interview follows standardized instruments adapted from validated tools such as the FIMA and FIMPsy, covering the following categories: outpatient medical care (e.g. physician visits), inpatient care (e.g. hospital days), (psychiatric) outpatient services of hospitals (e.g. long-term care services), therapeutic services (e.g. physiotherapy), medical devices (e.g. wheelchairs), pharmaceuticals (limited to psychotropic medications).

To validate and adjust for potential self-reporting bias, anonymized routine data will be obtained from participating statutory health insurance providers for approximately 15% of participants. The data will cover costs and health care as well as long-term care utilization in key healthcare sectors across two quarters before the enrollment quarter, the enrollment quarter, and the two quarters after the enrollment quarter (in total seven quarters).

Costs of care utilization will be determined using a combination of standard unit costs derived from publicly available national databases (e.g. Federal Statistical Office), routine claims data from health insurance providers, and internal cost data from the BRIDGE consortium for estimating the intervention’s implementation costs per patient. All costs will be adjusted to the year of analysis using inflation indices or healthcare-specific adjustment factors, as appropriate. The cost structure will include:

Intervention group (IG):K-11: Costs of the new BRIDGE interventionK-12: Costs of usual careTotal costs = K-1 = K-11 + K-12Control group (CG):K-21: Costs of usual careTotal costs = K-2 = K-21

### Operationalization of benefits

Benefits of BRIDGE (IG) and standard care (CG) are derived from the outcome evaluation. Three different benefits are estimated and analyzed separately:

N-1: achievement of the primary endpointN-2: index of achievement of selected secondary endpoints (sum-score); reduction of depressive symptoms, increase or maintenance of physical activity, increase or maintenance of physical functioning, increase or maintenance of quality of life, increase or maintenance of cognitive performance, reduction of perceived stress, increase or maintenance of emotional well-beingN-3: number of days in inpatient or day clinic stays

### Planned statistical analyses

Descriptive statistics will first be calculated for all outcome measures. To test the predefined hypotheses regression models — such as mixed models for repeated measures (MMRM) — will be employed, using appropriate link functions depending on the distribution of the outcome variables.

These regression models allow for flexible modelling of outcomes, accounting for potential confounding variables at both the individual and hospital levels — particularly in cases where randomization does not result in balanced groups or where selectivity analyses reveal relevant differences. Additionally, using a multilevel modelling approach enables to account for the clustering of participants within study centers.

The analytic strategy will follow an intention-to-treat (ITT) approach, enabling inclusion of participants despite missing data in the longitudinal follow-up and avoiding case-wise deletion due to attrition. Missing data will be handled using appropriate imputation or model-based estimation techniques to ensure robustness of the statistical analyses.

Subgroup analyses will be conducted for all primary and secondary endpoints to examine differences in intervention effects between the basic and intensive version of the BRIDGE intervention. This will involve estimating the interaction effect using a three-level grouping variable (IG-basic, IG-intensive, CG) to help identify the most appropriate target population for the intervention. Exploratory analyses will examine dose–response and adherence effects using data from the BRIDGE devices and app, which track the frequency and duration of exercise video use and video consultations. All statistical analyses will be conducted using the open-source software R (https://www.r-project.org/).

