### Sample size calculation

Recent meta-analyses evaluating the combined effects of behavioral therapy and physical exercise on depressive symptoms [28, 32] reported a significant overall effect size of Hedges’ g = − 0.47 (95% CI: − 0.83 to − 0.12, *p* = 0.005). This corresponds to a moderate reduction in depressive symptoms in favor of the combined intervention. However, to account for the lack of evidence in older, multimorbid adults, the more conservative power analysis was based on detecting a small to moderate effect size (Cohen’s d = 0.3; corresponding odds ratio ≈ 1.7) for the primary outcome of maintenance or improvement of inpatient treatment results with respect to depressive symptoms (binary: success vs. no success). Hence, the a priori sample size calculation resulted in a total of 800 participants accounting for an anticipated dropout rate of 20% and a statistical power of 90%. 533 participants will be allocated to the IG and 267 to the CG, following a 2:1 randomization ratio. This ratio was chosen to conduct a subgroup analysis within the IG comparing a basic version to an intensive version of the intervention.

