### Intervention

The BRIDGE intervention is a structured, manualized, interdisciplinary treatment program designed to support older, multimorbid participants with depressive symptoms during the critical transition from inpatient to outpatient care. It is embedded in an interdisciplinary and multiprofessional approach to optimally combine knowledge on psychological and exercise-based interventions for older adults with depressive symptoms. A distinctive feature of the BRIDGE intervention are the two interconnected and interacting core components, which comprise elements of behavioral activation and guided home-based physical exercise and are specifically developed and tailored for this vulnerable population. The BRIDGE blended care intervention spans 12 weeks per participant and is delivered using a modular, manualized treatment protocol, both in-person (e.g., home visits) and through a digital e-health solution (e.g., video consultation, PE videos, and mood monitoring) supported by a specifically developed workbook (BRIDGE workbook). Based on the severity of depressive symptoms, as assessed using the MADRS at T1 assessment, participants allocated to the IG will be assigned to either (i) a basic version (MADRS score < 20) or (ii) an intensive version (MADRS score ≥ 20). The two intervention versions are generally similar in content but comprise a different frequency of home visits and video consultations (Fig. 3 & 4).

i.**Basic** = 8 x obligatory consultations: 2 x home visits and 6 x video consultations, 12 guided PE videos;ii.**Intensive** = 12 x obligatory consultations: 4 x home visits and 8 x video consultations, 12 guided PE videos + 3 monthly check-up calls following the intervention period.

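### The basic-versus-intensive subgroup analysis splits only the intervention group by T1 MADRS, so without a severity term it can mistake prognosis for a difference in effect

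*Protocol article*

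**What the plan says.** **How the version is set.** The Intervention section makes the version a function of baseline severity: "Based on the severity of depressive symptoms, as assessed using the MADRS at T1 assessment", IG participants receive "a basic version (MADRS score < 20) or (ii) an intensive version (MADRS score ≥ 20". Nothing comparable is defined for the CG.

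**How the versions are compared.** Planned statistical analyses announces subgroup analyses for all primary and secondary endpoints, to "examine differences in intervention effects between the basic and intensive version of the BRIDGE intervention". The method is fixed there: "This will involve estimating the interaction effect using a three-level grouping variable (IG-basic, IG-intensive, CG) to help identify the most appropriate target population".

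**Weight given to it.** Sample size calculation explains the 2:1 allocation by this analysis: "This ratio was chosen to conduct a subgroup analysis within the IG comparing a basic version to an intensive version". Randomization and blinding gives the same reason.

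**Data available in the CG.** Outcome evaluation states: "Depressive symptoms will be assessed at all time points (T1 through T5) via both self-report (e.g., HADS) and clinician rating (e.g., MADRS"; it adds that both arms share the same time points. T1 MADRS is therefore scheduled in the CG too.

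**Adjustment.** Planned statistical analyses allows for confounders at patient and hospital level, with emphasis on chance imbalance and on findings of the selectivity analysis. It does not name T1 MADRS.

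**The concern.** A difference in intervention effect between two severity groups needs a control comparison inside each of them. The three-level variable taken alone does not provide one. IG-basic holds only patients below the cut-off, IG-intensive only those at or above it, and the CG holds both. Each contrast then adds a difference in prognosis to any difference in effect.

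The result is meant to help say who should receive the programme, and it determined the allocation ratio. If higher-MADRS patients do worse whatever their care, the basic version would look beneficial and the intensive version harmful. If they do better, the reverse would appear. Either way a target population could be named on prognosis alone.

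**Working it through.** **1. The plan's own figure.** No figure is given for the subgroup analysis; the only one is the total of 800. Inputs from Sample size calculation: d = 0.3 (odds ratio about 1.7), 90% power, 20% dropout, 2:1. Not stated and assumed here: two-sided alpha 0.05 and the control success rate p0. Converting d gives OR = exp(0.3π/√3) = 1.72. With p̄ = (2p1 + p0)/3,

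n(CG) = [1.96·√(1.5·p̄(1−p̄)) + 1.2816·√(p1(1−p1)/2 + p0(1−p0))]² / (p1 − p0)².

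At p0 = 0.45, p1 = 0.585 and n(CG) = 214, so the total is 642 and 642/0.8 = 803. At p0 = 0.40 and 0.50 the totals are 807 and 818. The 800 is reproduced within 3%. Evaluable patients: 0.8 × 800 = 640, or 427 IG and 213 CG.

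**2. What the three-level contrast estimates.** With one CG mean,

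(intensive − CG) − (basic − CG) = intensive − basic.

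The control group drops out. Now assume no BRIDGE effect. Let success be m below the cut-off and s at or above it, with a share q at or above. CG success is (1−q)m + qs, so

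- basic − CG = q(m − s)
- intensive − CG = −(1−q)(m − s)

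Both are zero only if m = s.

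**3. Size for a binary endpoint, no BRIDGE effect.** The success rates and q are assumptions; the documents give neither. The false-positive rate for basic versus intensive is Φ[(|m−s| − 1.96·SE0)/SE1], with SE0 pooled and SE1 unpooled.

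| m / s | q | CG success | n basic, intensive | OR basic v CG | OR intensive v CG | False positives |
|---|---|---|---|---|---|---|
| 60% / 45% | 50% | 52.5% | 213, 213 | 1.36 | 0.74 | 88% |
| 60% / 45% | 35% | 54.75% | 278, 149 | 1.24 | 0.68 | 84% |
| 60% / 50% | 50% | 55.0% | 213, 213 | 1.23 | 0.82 | 55% |
| 60% / 50% | 35% | 56.5% | 278, 149 | 1.15 | 0.77 | 51% |
| 60% / 55% | 50% | 57.5% | 213, 213 | 1.11 | 0.90 | 18% |

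First row in full: the odds are 0.60/0.40 = 1.50, 0.45/0.55 = 0.818 and, in the CG, 0.525/0.475 = 1.105. The ratios are 1.36 and 0.74. SE0 = √(2 × 0.525 × 0.475/213) = 0.0484 and SE1 = √((0.24 + 0.2475)/213) = 0.0478. Then (0.15 − 0.0948)/0.0478 = 1.15 and Φ(1.15) is about 0.88.

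A simulation (4,000 runs, overall success 60%, q = 30% or 50%) agrees. The false-positive rate is 18–20% at a severity odds ratio of 0.8, 45–51% at 0.67 and 90–93% at 0.5. With severity acting the other way (odds ratio 2.0) it is 88–93%, with the apparent benefit reversed. At odds ratio 1.0 it is 5%. With the CG also split and arm by stratum tested, it is 4–5% in every scenario.

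**4. MADRS change from T1.** Secondary outcomes lists reduction of depressive symptoms from T1 to T5, with MADRS as the clinician rating. Here the groups are formed on the starting value of the scale itself. Assume T1 mean 18, SD 7 and a T1-to-follow-up correlation r of 0.5 to 0.8. The truncated-normal means are 24.9 at or above 20 and 13.6 below, a gap of 11.3. Regression to the mean alone gives a larger fall in IG-intensive of 11.3 × (1 − r), which is 2.3 points at r = 0.8 and 5.6 at r = 0.5.

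**5. Power of the correct test.** Take a 50/50 split (213 IG and 107 CG per stratum), OR 1.72 in one stratum and 1.0 in the other. The SE of the log ratio of odds ratios is √Σ 1/(n·p(1−p)) = 0.337 at p0 = 0.5. Then ln 1.72/0.337 = 1.61 and power is Φ(1.61 − 1.96) = 0.36. At p0 = 0.6 the SE is 0.348 and power is about 0.35.

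**The case against.** **The three-level variable is not itself the fault.** Add the binary T1 MADRS stratum, defined in both arms, and there are four cells and four parameters: intercept, stratum, IG-basic and IG-intensive. The IG-basic coefficient is then IG versus CG below 20, the IG-intensive coefficient is IG versus CG at 20 or more, and their difference is the arm-by-stratum interaction. This is the same model in another parametrisation. The point stands: a reader might infer that the variable cannot estimate an interaction and has to be dropped, but that is true only if no severity term is in the model.

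**The analysis plan may supply that term.** The article allows confounder adjustment, its emphasis on imbalance and selectivity is not exclusive, and covariate lists usually belong in the analysis plan. This stands in part. But the article does fix the grouping with an unsplit CG. Severity differs between its levels by design, not through chance imbalance. Nor does any MADRS covariate suffice: in a simulation of MADRS change, a linear T1 term held the error near 5% when the relation was linear but left it at 51% in one assumed non-linear case.

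**The interaction may mean group by time.** Mixed models for repeated measures are named as an example. This does not rescue the contrast, because severity-selected groups can follow different courses untreated, as step 4 shows.

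**It is a subgroup analysis.** That stands and lowers the weight of the point. Still, it covers all endpoints, set the allocation ratio and feeds the target-population conclusion.

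**Conclusion.** The concern holds in a conditional form. As written, without a severity term, the subgroup analysis compares milder with more severe patients and can show a difference when BRIDGE does nothing. Under the assumed 10 to 15 point gap and 35 to 50% at or above the cut-off, apparent odds ratios versus CG are 1.15–1.36 for one version and 0.68–0.82 for the other, with false-positive rates of 51–88%. The rate is 18% with a 5-point gap and half the patients at or above the cut-off, and 5% with no gap.

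Two stronger readings are not supported. One is that the analysis must show a spurious difference. That needs T1 severity to predict the endpoint. For MADRS change from T1 this follows from selecting on the score. For maintenance or improvement on HADS from T2 to T4, the documents give neither the strength nor the direction of the relation. The other is that the trial's main result is compromised. The randomised IG-CG primary comparison does not use the version and is not affected.

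This should be corrected before results are seen, but it is not a defect of the primary analysis.

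**What to change.** - Define the T1 MADRS stratum (below 20, or 20 and above, as the protocol already does for the IG) in both arms.
- Fit arm + stratum + arm × stratum. Equivalently, keep the three-level variable and add the binary stratum as a covariate. In a repeated-measures model, cross the stratum with time wherever group is crossed with time.
- Report IG versus CG within each stratum, with intervals, and test the interaction.
- State that version and severity cannot be separated, because versions are not randomised. A difference between strata may reflect severity, the version received, or both.

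**Cost.** Wording in the protocol and analysis plan; T1 MADRS is already scheduled in both arms. The within-stratum comparison presumes that T1 MADRS is scored without knowledge of allocation. Ensuring that would be an operational step beyond this wording change.

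**Downside.** Power for the correct interaction test is about 35% for a ratio of odds ratios of 1.72 with a 50/50 split, so a null interaction should not be read as equal benefit.
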